#### Yoga teacher training

Approximately 24 yoga courses will be delivered within the trial by approximately 12 yoga teachers (i.e. each teacher delivering two separate courses). The teachers will all have the GYY qualification, appropriate insurance, and experience of working with older adults. They will also receive specific training in the trial background and procedures.

The GYY programme is copyrighted by the BWY and since 2017 has been providing training in GYY to qualified yoga teachers. Training for the GYY qualification takes place over approximately 12 months and covers the National Occupational Standards for understanding the principles of adapting physical activity for older adults and the planning, adaptation, and delivery of sessions to meet the requirements of participants with specific needs. This includes information on ageing, exercise barriers and motivators, ethical and legal responsibilities, the physiology of ageing and common chronic conditions, and how to modify yoga for different health states. After distance learning modules and face-to-face instruction, the teachers demonstrate their understanding through worksheets, multiple-choice questions, two case studies, designing a GYY programme, and being observed and assessed on their teaching of GYY sessions on two occasions.

To minimise inter-teacher variation and enhance the fidelity of intervention delivery, the yoga teachers will receive standardisation training from the trial team via a 1-day interactive workshop. The training will include clinical reasoning for the GYY programme, clarification of the standardised class content and structure, and practical delivery tips including intervention progression and provision of home practice sheets. It will also stress the importance of only allowing people in the trial’s intervention group to access the classes and other trial processes such as adverse event reporting and class attendance monitoring. To supplement this training day, teachers will also receive a standardised research training manual. The yoga teachers will have continued access to the intervention supervisors who developed the GYY teacher training course during their delivery of the 12-week intervention. The intervention supervisors will be responsible for supporting intervention delivery and sharing of best practice. Additional training and support will be available from the wider trial team as required, and this will be documented.

### Criteria for discontinuing or modifying allocated interventions {11b}

There are no specific criteria for discontinuing or modifying allocated interventions. Participants may choose to stop doing the yoga programme themselves for any reason or may be advised by their medical practitioner to discontinue practice due to ill health.

### Strategies to improve adherence to interventions {11c}

To optimise and encourage attendance, the teachers will be asked to contact participants who miss two consecutive classes without prior notification.

### Relevant concomitant care permitted or prohibited during the trial {11d}

Usual care for participants continues throughout the trial. There is nothing prohibited.

### Provisions for post-trial care {30}

Towards the end of their 12-session course, yoga participants will receive details of GYY or other suitable yoga classes that they could join on a self-pay basis. The control participants will receive the same information after completing the final follow-up questionnaire (12 months). There are no special compensation arrangements for those who suffer non-negligent harm from trial participation.

### Outcomes {12}

#### Primary outcome measure—EuroQoL 5 Dimensions (5L) Score (EQ-5D-5L)

The primary outcome will be health-related quality of life (HRQoL) as measured by the EQ-5D-5L utility score [24]. This will be assessed according to current EuroQol guidance [25] at baseline and 3, 6, and 12 months after randomisation. The primary endpoint will be the overall difference over the 12 months. There is a valuation set for the EQ-5D-5L available for England [26]; however, this is currently under revision. Meanwhile, the UK’s National Institute for Health and Care Excellence (NICE) recommends that utility values should be calculated using the crosswalk developed by van Hout et al. [27]. Utility scores will be calculated following the NICE guidance at the time of the analysis.

The EQ-5D™ is a widely used self-reported generic measure of HRQoL which comprises two parts: the classification of 5 dimensions of health (mobility, self-care, usual activities, pain/discomfort, and anxiety/depression) and a visual analogue scale (VAS), which records participants’ overall evaluation of their health on a scale from 100 (best imaginable health) to 0 (worst imaginable health). The EQ-5D has been validated in many different patient populations including diabetes, cardiovascular problems, chronic obstructive pulmonary disease, cancer, chronic pain, and rheumatoid arthritis. There are currently two versions of the instrument that can be used for adults: the original EQ-5D-3L with five dimensions of health and 3 levels of problems, and the more recent EQ-5D-5L that has the same five dimensions of health and 5 levels of problems (1 = no problems, 2 = slight problems, 3 = moderate problems, 4 = severe problems, and 5 = unable/extreme problems). The EQ-5D-5L helps overcome problems with ceiling effects and has greater sensitivity [24]. It showed evidence of good sensitivity in our pilot trial [21] and has been the primary outcome measure in other primary care-based multimorbidity trials [28]. Besides being used as the primary outcome measure in the analysis, the EQ-5D-5L will be also used to estimate QALYs for our economic evaluation.

#### Secondary outcome measures

The following are the secondary outcome measures:
HRQoL at 3, 6, and 12 months after randomisation using the EQ-5D-5L utility score.HRQoL at 3, 6, and 12 months and overall using the PROMIS-29 [29].Depression severity at 3, 6, and 12 months and overall using the Patient Health Questionnaire-8 [30].Anxiety severity at 3, 6, and 12 months and overall using the Generalised Anxiety Disorder-7 [31].Loneliness at 3, 6, and 12 months and overall. Four questions are used to capture different aspects of loneliness. The first three questions are from the University of California, Los Angeles (UCLA) 3-item loneliness scale [32]. The wording of the UCLA questions and response options are taken from the English Longitudinal Study of Ageing. The last is a direct question about how often the respondent feels lonely.The incidence of falls over 12 months assessed via self-report at 3, 6, and 12 months.Adverse events over 12 months.Resource use data will be collected to inform the economic evaluation from patient questionnaires and GP practice records (i.e. medication data).

#### Process evaluation

A qualitative process evaluation will be undertaken to (i) identify, describe, and explain the barriers and facilitators to set-up, recruitment, and trial processes; (ii) describe recipients’ and providers’ experiences of the yoga intervention and study process; and (iii) identify optimal implementation strategies for embedding and normalising the yoga intervention in preparation for a wider roll-out. Data will be collected during the pilot and main trial phases, via semi-structured interviews with both intervention and control group trial participants (*n* = 18–20), trial decliners (*n* = 3–4), and yoga teachers (*n* = 10–12), as well as from observations of standardisation training sessions and yoga classes. A subset of trial participants (*n* = 8–12) will be invited to take part in a second interview approximately 6 months after their first interview, to explore any long-term impact of their trial participation. Pilot phase yoga teachers will be interviewed once per 12-week course they deliver, and their feedback used to optimise the standardisation training and intervention delivery for main phase yoga teacher, main phase teachers will be interviewed once. A subset of trial staff (*n* = 1–5) may also be interviewed to inform intervention implementation. Interviews will be conducted face-to-face or by telephone or video conference.

#### Other outcomes

Adherence to the supervised GYY classes will be recorded by the yoga teachers using class attendance registers. We will also ask participants to report any other supervised or self-managed yoga practice in the follow-up questionnaires. Treatment fidelity will be assessed via observation of a yoga session at each site by the yoga intervention supervisors (LB and JH) and through discussions with teachers as part of the process evaluation. Socio-demographic measures (age, gender, ethnicity, residential status, employment status, smoking status) and details of medical conditions (assessed using an adapted Bayliss measure of illness burden [33]) will be collected at baseline. Participant beliefs and preferences for the GYY programme and usual care will be assessed at baseline and 12 months.

### Participant timeline {13}

See Fig. 2 for the participant’s timeline through the trial.

**Fig. 2 Fig2:**
[figure not shown]
Flow diagram illustrating the practice and patient recruitment, intervention delivery, and follow-up

### Sample size {14}

Walters and Brazier [34] in a review paper of the EQ-5D-3L found a difference of 0.074 (mean) or 0.081 (median) to be a minimum clinically important difference among a variety of patients, whilst McClure and colleagues found a difference of 0.063 (mean) or 0.064 (median) for the EQ-5D-5L using simulated data [35]. To be conservative, we took the lowest estimate (0.06) with an estimated standard deviation of 0.20 [21]. Accounting for loss to follow-up of 20%, we need to recruit and randomise 586 participants for the study to have 90% power with 5% significance (two-sided).

Although this is an individually randomised trial, there is a possibility of potential clustering within the intervention arm by yoga class. If we assume an intraclass correlation coefficient of 0.04 and an average class size of 12 in the intervention arm, then with the proposed sample size, we would still retain 84% power to detect the same magnitude of effect (ceteris paribus). In this calculation, we considered the level of clustering at the yoga class level, rather than at the level of the yoga teacher, since we believe this will be the most influential level of clustering. Accounting for potential clustering within the intervention arm only leads to small reductions in power, which could potentially be recovered in the analysis of the repeated measures which is not currently accounted for in the sample size calculation.

### Recruitment {15}

#### Recruitment of practices

General practices that are potentially interested in taking part in the trial will be identified with help from the NHS Clinical Research Networks in England, the Health and Care Research Wales Support and Delivery Centre, and the Scottish Primary Care Network. These nationwide networks facilitate clinical research by identifying and recruiting general practices and providing resources to help practices do research. Trial coordinators will liaise with key stakeholders at the practice (e.g. practice manager, GPs) to explain the requirements of the study. The practice manager or lead GP will sign a practice-level agreement.

#### Recruitment of participants

The main method of participant recruitment will involve inviting potentially eligible patients who are identified from searching general practice databases at approximately 24–36 practices. Other methods that may be used if required include local media advertising, recruiting from patient networks, and inviting potentially eligible patients from previous studies that have been coordinated by York Trials Unit.

For the main recruitment method, each participating practice will be asked to search their practice database using an electronic search process provided by the research team to identify potentially eligible patients who are aged 65 years or older and have two or more chronic conditions as defined by the inclusion criteria. If there are more potentially eligible patients than required (e.g. > 500 for a recruitment mail-out from a single practice required to cover one course/site), a sub-sample of these patients will be randomly selected. GPs will be asked to review the resulting list to screen out patients meeting the exclusion criteria. The practice or Docmail (a third-party information handler) will mail out a recruitment pack to the remaining patients, which will include a covering invitation letter, a participant information sheet (which includes a link to an audio version on the trial website), a consent form, a screening questionnaire, and two prepaid envelopes for returning the completed forms. If the patient is screened as eligible, a study investigator will notify the patient’s GP and ask them to confirm the patient’s suitability for participation. Eligible patients will then be sent a baseline questionnaire to complete and return by a specified date. This questionnaire will collect data on socio-demographics measures, primary and secondary outcome measures, and preferences/beliefs for the treatments on offer in the trial.

##### Alternative process due to COVID-19 restrictions

The COVID-19 pandemic has made the above postal consent and questionnaire data collection processes difficult to implement because the trial team has been required to work from home. Therefore, where necessary, consent will be completed electronically by potential participants via an online form, participants will be contacted by a study investigator to collect screening and baseline questionnaire data via telephone, and this questionnaire data will be entered electronically via an online form by a study investigator.

#### Recruitment of yoga teachers

Yoga teachers who are potentially interested in taking part in the trial will be identified by the trial’s yoga consultants (LB and JH). The consultants are aware of who has completed the GYY teacher training course and where they are based. The consultants and trial coordinators will liaise with potential teachers to explain the requirements of the study. Each teacher will sign a contract with the University of York.

### Assignment of interventions: allocation

#### Sequence generation {16a}

The randomisation is stratified by site using varying block sizes and allocation ratios.

#### Concealment mechanism {16b}

Participants will be randomised via a central, computer-based randomisation system, designed and managed by York Trials Unit. Since a group of participants is assigned to a treatment group in one go as opposed to being randomised one-by-one, as described in the next section, the allocation sequence cannot be predicted in advance.

#### Implementation {16c}

When enough patients (ideally 20–30) have provided baseline data and stated their availability for a particular GYY course at a particular site, they will be randomised collectively by a member of the research team using the randomisation system. The block of patients will be allocated to either the intervention or control group in a ratio that can vary and is specified to ensure that the maximum class size is not exceeded (12–15 participants for face-to-face and 12 for online to the intervention group, and the rest to control). We are targeting an overall allocation ratio of 1:1.

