### Statistical methods

#### Statistical methods for primary and secondary outcomes {20a}

Statistical analyses will be described in detail in a statistical analysis plan (SAP) that will be agreed upon with the Trial Steering Committee before all data has been collected. Any subsequent amendments will be clearly stated and justified. The trial will be reported in accordance with the Consolidated Standards of Reporting Trials (CONSORT) guidelines for clinical trials [36]. Baseline data will be summarised using descriptive statistics with no formal statistical comparisons of the baseline data undertaken. All analyses will be conducted on an intention-to-treat basis and using two-sided significance tests at the 5% significance level, unless otherwise stated.

The primary outcome will be analysed using a linear mixed model, including all available follow-up time points. The model will adjust for EQ-5D-5L at baseline and include as fixed effects: time point, trial arm, arm by time interaction, and other covariates specified in the SAP. Patient (to account for the repeated measures) and site will be included as random effects. The overall difference between the two groups over the 12 months from randomisation will be the primary endpoint, but differences at each time point will be extracted for secondary investigations aimed at determining the potential pattern of change. Adjusted mean differences will be presented with an associated 95% CI and *p* value. Different covariance patterns for the repeated measurements will be explored, and the most appropriate pattern will be used for the final model. Model assumptions will be checked, and if they are in doubt, transformations of the outcome data will be considered. Analyses to account for possible clustering by yoga class will also be undertaken by including the class as a random effect, nested within the treatment arm. We shall explore the impact of differing modes of delivery (face-to-face, or online) within subgroup analyses.

The anxiety, depression, loneliness, and PROMIS-29 data will be analysed in the same way as described for the primary outcome. The number of falls experienced by participants over the 12 months will be analysed using a negative binomial regression model. The number and type of serious and non-serious adverse events will be summarised descriptively by randomised group.

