#### Interim analyses {21b}

There are no planned interim analyses for the trial or stopping guidelines. There is, however, an internal pilot study from which data will contribute to the final analyses. The primary reason for this pilot study will be to check the assumptions about recruitment and feasibility of the trial. The period covering the two waves of yoga courses at the four pilot sites will form the internal pilot phase. Descriptive statistics will be used to evaluate the four following progression criteria and inform study continuation beyond the pilot phase:
Intervention provision
Green: 3–4 sites offering their first group yoga session within 3 weeks after randomisationAmber: 1–2 sites offering their first group yoga session within 3 weeks after randomisationRed: 0 sites offering their first group yoga session within 3 weeks after randomisationIntervention acceptability
Green: ≥80% for overall class attendance rateAmber: 65–80% for overall class attendance rateRed: < 65% for overall class attendance rateRecruitment
Green: 3–4 sites recruited ≥20 patients each within 4 monthsAmber: 1–2 sites recruited ≥20 patients each within 4 monthsRed: 0 sites recruited ≥20 patients each within 4 monthsSix-month follow-up
Green: ≥80% completion of the EQ-5D-5LAmber: 65–80% completion of the EQ-5D-5LRed: < 65% completion of the EQ-5D-5L

If any criteria are graded as amber, a rescue plan will be developed outlining steps to be taken to improve intervention provision, recruitment, class attendance, and/or outcome follow-up (as appropriate) and will be agreed upon with the Trial Steering Committee and the funder. If all the progression criteria are failed (red), then the trial will not continue beyond the pilot phase.

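### Allocation ratios are set per course batch, but the stated stratifier and the only design factor named in the primary model are site, so the model does not condition on the unit randomised

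*Protocol article*

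**What the plan says.** Under Implementation {16c}, once about 20 to 30 patients are available for a given course at a given site they are randomised in one go, "in a ratio that can vary and is specified to ensure that the maximum class size is not exceeded". The intervention group takes 12 to 15 people for face-to-face delivery or 12 for online delivery. Everyone else in the batch becomes a control. The overall target is 1:1.

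Sequence generation {16a} describes this as follows: "The randomisation is stratified by site using varying block sizes and allocation ratios".

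Site and batch are not the same thing everywhere. Interim analyses {21b} refers to "The period covering the two waves of yoga courses at the four pilot sites", so each pilot site contributes more than one batch. Yoga teacher training expects about 24 courses from about 12 teachers, two courses each.

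The primary model in {20a} has fixed effects for baseline EQ-5D-5L, time, arm, arm by time, and further covariates to be named in the SAP. On the design structure it says: "Patient (to account for the repeated measures) and site will be included as random effects". Yoga class enters as a random effect within arm in an additional analysis. Delivery mode appears only as a subgroup analysis.

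**The concern.** When the chance of receiving yoga differs between batches, allocation is independent of prognosis only within a batch. A batch with a high yoga share contributes more to the intervention mean, and a batch with a low share contributes more to the control mean. If those batches also differ in EQ-5D-5L level, part of that difference appears as a treatment effect. A site intercept cannot separate two waves at the same site. Because it is a random effect it is also shrunken, so it removes differences between sites only in part.

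The protocol itself offers a route for ratio and outcome level to move together. The class cap depends on delivery mode, online delivery is tied to pandemic restrictions, and the eligibility section adds practical barriers that apply only to online classes. Mode can therefore shift the ratio, the calendar period and the recruited population at once. What is at stake is a systematic component in the primary estimate that a larger sample would not remove if the association is systematic.

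**Working it through.** **1. The plan's own figures reproduce.** Inputs from Sample size {14}: "we took the lowest estimate (0.06) with an estimated standard deviation of 0.20", 90% power, two-sided 5%, 20% loss.
- Per arm: 2 × (1.960 + 1.282)² × 0.20² / 0.06² = 233.5, so 234. In total, 468 / 0.8 = 585 (587.5 with a t-test). Stated: 586.
- With "an intraclass correlation coefficient of 0.04 and an average class size of 12 in the intervention arm", the design effect is 1 + 11 × 0.04 = 1.44 in that arm only. Analysed: 586 × 0.8 = 468.8, or 234.4 per arm. SE = 0.20 × √((1.44 + 1)/234.4) = 0.0204. Power = Φ(0.06/0.0204 − 1.96) = 83.7%. Stated: 84%.

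**2. Range of ratios the rules allow.** With 12 to yoga, a batch of 20 gives 12/20 = 60% and a batch of 30 gives 12/30 = 40%. With 15 to yoga, a batch of 20 gives 75%. The average batch is 586/24 = 24.4, so 12 to yoga is 49%.

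**3. Bias at a site with two batches.** Let d be the difference in EQ-5D-5L level between batches that remains after adjustment (assumed). With site as the only design factor:

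bias = d × (share of the yoga group from batch 1 − share of the control group from batch 1)

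| Batch 1, batch 2 (yoga/total) | Yoga share − control share | d = 0.02 | d = 0.05 | d = 0.05, as % of 0.06 |
|---|---|---|---|---|
| 12/24, 12/24 | 12/24 − 12/24 = 0 | 0 | 0 | 0% |
| 12/22, 12/26 | 12/24 − 10/24 = 0.083 | 0.0017 | 0.0042 | 7% |
| 15/24, 12/24 | 15/27 − 9/21 = 0.127 | 0.0025 | 0.0063 | 11% |
| 12/20, 12/30 | 12/24 − 8/26 = 0.192 | 0.0038 | 0.0096 | 16% |
| 15/20, 12/30 | 15/27 − 5/23 = 0.338 | 0.0068 | 0.0169 | 28% |

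These become trial-wide figures only if every site has the same pair with the gap in the same direction.

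**4. Trial-wide simulation.** Assumptions: 12 sites with two batches of 20 to 30 each, 12 or 15 to yoga, residual SD 0.20, true effect zero, 4,000 runs per scenario. Batch levels have SD 0.02, 0.04 or 0.06 and a nominal correlation with the batch's ratio. Site was fitted as a fixed effect, with no baseline adjustment.

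| Correlation | Bias, site only | Type I error, site only |
|---|---|---|
| None | about 0 | 4.2–5.0% |
| 0.5 | 0.002–0.007 | 5.2–7.1% |
| 1.0 | 0.0045–0.012 | 5.5–11.1% |

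With batch in the model, bias was −0.0005 to 0.0006 and type I error 4.2–5.2% throughout. At batch SD 0.02 and correlation 0.5 both models gave 5.2%, so no inflation is visible there.

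**5. Precision.** The mean model SE was 0.0167 with batch, against 0.0166 to 0.0170 with site.

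**6. Effect of a random site intercept.** With a random intercept, and d taken as what remains after baseline adjustment, the 12/20 and 12/30 pairing with d = 0.05 still gives about 0.010. Where each site has a single batch, shrinkage leaves about 0.006 for the same difference.

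**The case against.** A reader might infer that the model adjusts for nothing but site. The text does not support that. Baseline EQ-5D-5L is in the model and is collected before each batch is randomised, so it absorbs part of any batch difference present at that time. Further covariates are left to a SAP that is not shown and may include batch, wave or mode. This stands and narrows the point. It does not dispose of it: the protocol itself fixes the stratifier and the random effects, and these do not match its own randomisation procedure. Baseline adjustment also cannot remove shifts that arise during follow-up.

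A reader might also infer that bias is automatic. It is not. It needs ratios that vary and that go with outcome level, and the documents contain no evidence of such a link beyond the mode-dependent caps. Nor are the extreme ratios the plan. A 15:5 split runs against the 1:1 target, and a face-to-face batch of 24 to 30 can be split 12:12 to 15:15 within the stated caps. With a random site intercept and an assumed residual batch SD of 0.025, always sending 12 to yoga gives a bias of about 0.0025 at correlation 0.5 and 0.005 at correlation 1. Splitting 1:1 wherever a cap of 12 allows roughly halves this. Two waves are documented only for the four pilot sites, and elsewhere a site may have one course.

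The planned class random effect does not answer the point. Trial classes contain intervention participants only, so it does not compare arms within a batch.

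**Conclusion.** The mismatch is real: the ratio is set per batch, while the stratification statement and the primary model name site. Whether it biases the estimate depends on quantities the documents do not give. The expected bias is about zero if ratio and batch level are unrelated. It is roughly 0.002 to 0.007 (4% to 12% of 0.06) for an assumed batch SD of 0.02 to 0.06 and correlation of 0.5. It is about 0.01 (16%) if 12/20 and 12/30 batches are paired at every site with a residual difference of 0.05. The simulated range omits baseline adjustment, which would lower it, and treats site as fixed, which hides the part that shrinkage leaves. The figure of 28% needs a 3:1 batch at every site and should not be read as what to expect. The stated sample size and power are unaffected. This is a worthwhile, nearly free improvement. The documents do not support calling the planned analysis invalid.

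**What to change.** In Sequence generation {16a}, name the batch (site by course or wave) as the randomisation stratum. In {20a}, for the primary outcome and the secondary outcomes analysed with the same mixed model, use a fixed effect for batch in place of the site random effect. Each batch belongs to one site, so site differences are covered. Record the batch identifier and its allocation ratio in the analysis dataset.

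The cost is a sentence in each section and about 24 batch parameters against some 469 participants expected at analysis. Precision loss is negligible and 586 is unchanged. The class random effect can stay as the additional analysis already planned. Moving it into the primary model is a separate decision that this argument does not support; allowing for class clustering is what takes the stated power from 90% to 84%.
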